### Randomisation and allocation

The study subjects who satisfy the eligibility criteria will be randomised using a computer program at an independent centre (Kyung Hee University Center for Clinical Research and Drug Development; KCRD). Block randomisation with block size of 4 will be performed. The study subjects will be assigned to one of two groups with a 1:1 allocation ratio by investigator in each study site. Random numbers will be sent to each centre, and a randomisation table will be maintained by KCRD during the research period. Opaque sealed envelopes containing serial numbers will be delivered to each centre. The randomisation table kept in an opaque sealed envelope by the contract research organisation (CRO; KCRD) should be opened according to Standard Operating Procedures (SOPs).

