### Sample size

Sample size calculations were performed to determine the number of participants needed to detect the effect sizes. We obtained an effect size from the previous study and based on the agreement of experts [14]. The results from the previous study were used to calculate the standard deviation [15]. The mean difference and standard deviation of the scoring atopic dermatitis (SCORAD) index were 10 and 13.576, respectively. The following formula was used to estimate the sample size.

$$\begin{array}{ll} n & =\frac{2{\left(z_{\alpha /2}+z_{\beta }\right)}^{2}\sigma^{2}}{{\left(\mu_{c}-\mu_{t}\right)}^{2}}\\ & =\frac{2\times {\left(1.96+0.84\right)}^{2}\times 13.576^{2}}{10^{2}}\\ & =28.932 \end{array}$$

The calculation was performed using 80% power, a 5% significance level, and a 10% dropout rate. The required sample size is approximately 33 participants for each group. Therefore, a total of 66 participants are needed for this trial.

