### Statistical analysis

#### Efficacy assessment

Statistical analyses will be performed for both the ITT (intention-to treat, all randomly assigned participants) and PP (per-protocol, participants completed the trial without any protocol deviations) data sets. The missing values will be imputed by the last observation carried forward (LOCF) method. The continuous variables will be displayed as the mean ± SD(standard deviation), and the categorical variables will be displayed as the n (%). The baseline characteristics will be compared by either a Student’s *t*-test for continuous variables or the χ^2^ test (Fisher’s exact test will be used when the expected value is < 5) for the categorical data. Alternatively, McNemar’s test will be used if the normality assumption is not satisfied for the continuous variables. For the primary outcome measures, the mean differences from the baseline values to the end of treatment will be compared using an independent T-test.

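### Block-randomised numbers go to each of three centres, but the primary t-test has no centre term; if blocks are within centre and centres differ, the test is mildly conservative

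*Protocol article*

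**What the plan says.** All references are to the protocol article.

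- **Randomisation and allocation.** "Block randomisation with block size of 4 will be performed". Participants are "assigned to one of two groups with a 1:1 allocation ratio by investigator in each study site". On supply: "Random numbers will be sent to each centre, and a randomisation table will be maintained by KCRD during the research period"; sealed envelopes with serial numbers also go to each centre. The section does not say that the list is stratified by centre or that blocks are formed within centre.
- **Statistical analysis, Efficacy assessment.** For the primary outcome, "the mean differences from the baseline values to the end of treatment will be compared using an independent T-test". Centre does not appear in this section.
- **Sample size.** "The mean difference and standard deviation of the scoring atopic dermatitis (SCORAD) index were 10 and 13.576, respectively". The result after allowing for dropout is 33 per arm: "The required sample size is approximately 33 participants for each group". It assumes 80% power, a two-sided 5% level and 10% dropout. No between-centre component of variance is given.
- **Primary outcome measurement.** The endpoint is the change in SCORAD from Visit 2 to Visit 5.

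**The concern.** If each hospital works through its own sequence of blocks of 4, the arms are held nearly equal in size within each hospital. Differences between hospitals in mean SCORAD change then largely cancel out of the treatment comparison, so the true variance of the treatment difference contains little of them. A pooled two-sample t-test does not use this. It leaves the between-hospital variation in its error term, so its standard error is larger than the actual sampling variation of the estimate. Intervals come out too wide, the type I error falls below the nominal 5%, and some power is given up.

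Hospitals could differ in the amount of change through case mix, routine care or scoring that shifts over time. Recruitment through physicians, posters and newspaper advertisements makes differences in case mix plausible. At stake is efficiency in a trial planned for just 80% power.

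This is not a detail left to an analysis plan that is not shown. The article names the primary test, and that test has no place for centre.

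**Working it through.** **1. The plan's own figure.** Inputs from the Sample size section: difference 10, SD 13.576, two-sided 5%, power 80%, dropout 10%.

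n per arm = 2 × (1.96 + 0.84)² × 13.576² / 10² = 28.90 with the rounded z values. Unrounded z values give the printed 28.932. Rounded up, this is 29; 29 / 0.9 = 32.2, so 33 per arm and 66 in total. The stated size reproduces.

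**2. Assumption.** Let c be the share of the variance of SCORAD change that lies between centres. The article gives no value, so c is varied. The SD of 13.576 is taken as the total SD.

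**3. Hand calculation, blocks within centre.** Expected completers per arm: 33 × 0.9 = 29.7.

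- Standard error used by the t-test: 13.576 × √(2/29.7) = 3.523.
- True standard error: 3.523 × √(1 − c).
- Overstatement: 1/√(1 − c) − 1.
- Actual alpha: 2 × [1 − Φ(1.96/√(1 − c))].
- Power of the t-test: Φ[(10 − 1.96 × 3.523) / true SE].
- Power of the adjusted model: Φ[10 / true SE − 1.96].

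| c | True SE | SE overstated | Actual alpha | Power, t-test | Power, adjusted |
|---|---|---|---|---|---|
| 5% | 3.434 | 2.6% | 4.4% | 81.6% | 83.0% |
| 10% | 3.342 | 5.4% | 3.9% | 82.3% | 84.9% |

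For c from 2% to 20% the standard error is overstated by 1% to 12%.

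**4. Check by simulation.** Step 3 uses the normal approximation and ignores the degrees of freedom spent on centre. A simulation with 100,000 runs per setting removes both simplifications. It has 60 completers, three equal centres of 20, exact 1:1 balance within centre, no treatment-by-centre interaction and total SD 13.576. The adjusted analysis is a linear model with treatment and centre.

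| c | Actual alpha, t-test | Power, t-test | Power, adjusted | Points forgone |
|---|---|---|---|---|
| 0% | 4.9% | 80.0% | 79.9% | about 0 |
| 1% | 4.9% | 80.3% | 80.6% | 0.2 |
| 5% | 4.4% | 80.6% | 82.0% | 1.4 |
| 10% | 3.9% | 81.3% | 84.1% | 2.8 |
| 20% | 2.9% | 82.5% | 88.1% | 5.5 |
| 30% | 1.8% | 83.8% | 91.6% | about 8 |

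Points forgone are taken before rounding. The adjusted model held its type I error at 4.8 to 5.0% throughout. In the runs with no treatment effect, the t-test's mean standard error against the actual SD of the estimate was 3.49 against 3.43 (c = 5%), 3.50 against 3.33 (10%) and 3.51 against 3.14 (20%).

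**5. Cost when centres do not differ.** With 30 per arm, noncentral-t power is 80.10% for the t-test (58 df) and 80.06% for the adjusted model (56 df), a loss of less than 0.1 point.

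**6. Blocks not within centre.** Imbalance of arms across centres is then part of ordinary randomisation variability, which the t-test's standard error already covers. The overstatement in steps 3 and 4 does not arise.

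**The case against.** The strongest case against the point has four parts.

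- **The premise is inferred.** A single central list in blocks of 4, divided among hospitals by number range, also fits the text. This stands. A reader might infer that the standard error certainly does not match the design, or that centre must be in the model under either scheme. The article supports neither, because without blocking within centre the t-test is valid.
- **The size is assumed.** A stable additive scoring offset between raters or hospitals cancels in a change score, so rater-scored SCORAD alone does not imply a large centre share. Only differences in the amount of change count. This stands, and at a share of 0 to 1% there is almost nothing to gain.
- **The direction is safe.** A reader might infer that the trial is underpowered or at risk of a false positive. Neither follows. The t-test's power was 80.0% to 83.8% across the simulated settings, and its type I error only falls. Power is forgone relative to a better model, not relative to the plan.
- **The calculation is idealised.** Equal recruitment gives 22 per centre, which leaves an incomplete block of 4, and dropout disturbs the balance further. This stands but changes the figures only slightly.

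None of this removes the core of the point: the primary test is stated, it omits centre, and including centre costs almost nothing.

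**Conclusion.** The point holds as a conditional and modest loss of efficiency. It requires that blocks are formed within centre, which is the natural reading but is not stated, and that centres differ in mean SCORAD change, which is plausible but not quantified.

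Under an assumed 5 to 10% between-centre share, the standard error is overstated by about 3 to 5%, the actual alpha is about 4.4 to 3.9%, and about 1.4 to 2.8 points of power are forgone. Over assumed shares from 0 to 30%, the power forgone runs from about nil to about 8 points. The statement that power stays at about 80% or above rests on 13.576 being the total SD and on about 30 completers per arm. The t-test is valid or conservative under both readings of the randomisation, so a positive result would not be in doubt on this account, and the sample size need not rise.

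**What to change.** 1. In the Randomisation and allocation section, state that blocks are formed within centre, or that they are not.
2. In the Efficacy assessment section, replace the independent t-test for the primary outcome with a linear model of SCORAD change from Visit 2 to Visit 5, with treatment and centre (three levels) as fixed effects. Report the treatment difference with its 95% confidence interval from that model.
3. Make the change before unblinding, so that the centre term cannot look chosen from the results.

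The cost is one sentence, one model term and two degrees of freedom (58 to 56 with 60 completers). No extra participants or data are needed. If the blocks turn out not to be within centre, the same model remains acceptable, and its only purpose is precision.

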### Blinding

Both the investigator and the subject will be blinded regarding the assignment of the study drugs. The CRO of the sponsor will label the investigational drugs using the randomisation code number. The labelled experimental products will be provided to the trial sites by the CRO.

### Treatment protocol

The participants will receive KM110329 or a placebo drug for eight weeks. They will take 2 tablets by mouth with water twice a day after meals.

### Interventions

Hanpoong Pharm and Foods Co., Ltd. produced the KM110329 and the placebo according to Korea Good Manufacturing Practice (KGMP) standards. KM110329 is a brown-coloured, round-shaped tablet. It is compound of Rubi Fructus, Houttuyniae Herba, Rehmanniae Radix, and Betulae Platyphyllae Cortex. The placebo medicine is made of lactose, corn starch and food colouring, and it has a similar appearance, shape, weight, taste and colour as KM110329.

### Primary outcome measurement

The primary outcome in the present study is the change in the SCORAD index between the baseline (Visit 2) and after the treatment (Visit 5). The SCORAD index is a clinical tool for assessing the severity of atopic dermatitis as objectively as possible. The SCORAD index will be measured at every visit.

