**Methods/design:**

This study is a randomised, double-blind, placebo-controlled and multicentre trial of KM110329. For this study, we will recruit 66 atopic dermatitis patients of both sexes, with ages ranging from 18 to 65, from three university hospitals. The participants will receive either KM110329 or a placebo twice a day for 8 weeks. The primary end point will be a change in the scoring atopic dermatitis (SCORAD) index. The secondary end points will include changes to the dermatology life quality index (DLQI) and transepidermal water loss (TEWL), among others. The outcomes will be measured at every visit. The study will be continued for 8 weeks and will include five visits with each subject (at screening and at 0, 1, 4 and 8 weeks).

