### Inclusion and exclusion criteria

Inclusion criteria

1. Men and women ages 18 to 65 years

2. Individuals diagnosed with atopic dermatitis according to the criteria of Hanifin and Rajka

3. Individuals with mild to moderate atopic dermatitis (objective SCORAD ≤ 40)

4. Written informed consent for participation in the trial

Exclusion Criteria

1. Severe skin disease other than atopic dermatitis

2. Secondary infection with bacteria, fungi, or virus

3. Uncontrolled hypertension (SBP > 145 mmHg or DBP > 95 mmHg)

4. Severe liver disability (2.5-fold the normal high range value for ALT, AST)

5. Severe renal disability (sCr > 2.0 mg/dl)

6. Women who are pregnant, lactating, planning a pregnancy or women of child-bearing age who do not agree to use proper contraception

7. Use of oral steroids, oral antibiotic or other immunosuppressants within the past 4 weeks

8. Treated by systemic photochemotherapy within the past 4 weeks

9. History of drug abuse

10. Hypersensitivity to Rubi Fructus, Houttuyniae Herba, Rehmanniae Radix, or Betulae Platyphyllae Cortex

11. Use of other investigational products within the past two months

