### Secondary outcome measurement

Secondary outcome measurements include the change in the Dermatology Life Quality Index (DLQI), the total IgE level, eosinophil counts, IL-4, IL-5, IL-13, TEWL (Transepidermal Water Loss), hydration in the stratum corneum, and KiFDA-HM-AD. The study schedule is detailed in Table 1.

**Table 1 T1:** Study schedule of KM110329 clinical trial (8 weeks)

	**Screening**	**Treatment period**			
	**Visit 1**	**Visit 2**	**Visit 3**	**Visit 4**	**Visit 5**
	**(D − 7)**	**(D 0)**	**(D 7)**	**(D 28)**	**(D 56)**
**Informed consent**	**√**				
**Demographic characteristic eristic**	**√**				
**SCORAD index**	**√**	**√**	**√**	**√**	**√**
**Dermatology Life Quality Index**		**√**	**√**	**√**	**√**
**KiFDA-HM-AD**		**√**	**√**	**√**	**√**
**Laboratory tests**^ **1** ^	**√**	**√**			**√**
**Test for chronic hepatitis**^ **2** ^	**√**				
**Drug use history**	**√**				
**Concomitant medication**	**√**	**√**	**√**	**√**	**√**
**Pregnancy test**	**√**	**√**	**√**	**√**	**√**
**Medical/drug use history**	**√**	**√**	**√**	**√**	**√**
**Adverse event**			**√**	**√**	**√**
**Compliance calculation**			**√**	**√**	**√**
**Inclusion/exclusion criteria check**	**√**				
**Randomisation**		**√**			

^1^CBC (RBC, Hb, Hct, WBC, Platelet, ESR), Immunological tests (Eosinophil, IgE, IL-4, IL-5, IL-13), Liver function tests (AST, ALT), Renal function tests (BUN, Creatinine).

^2^Anti-HBs, HBsAg.

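### The primary analysis uses one of two pre-dose SCORAD scores, and only as a raw change; a model with both as covariates would probably be more precise at almost no cost

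*Protocol article*

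**What the plan says.** - The Primary outcome measurement section fixes the endpoint as "the change in the SCORAD index between the baseline (Visit 2) and after the treatment (Visit 5", and adds: "The SCORAD index will be measured at every visit".
- Table 1, "Study schedule of KM110329 clinical trial (8 weeks", ticks SCORAD at all five visits. Visit 1 (D−7) and Visit 2 (D0, randomisation) both precede treatment. The article describes no run-in treatment between them.
- Table 1 ticks the eligibility check at Visit 1 only. One entry criterion is "Individuals with mild to moderate atopic dermatitis (objective SCORAD ≤ 40".
- The Efficacy assessment section states the primary analysis: "the mean differences from the baseline values to the end of treatment will be compared using an independent T-test". No covariate is named.
- The Sample size section gives the inputs: "The mean difference and standard deviation of the scoring atopic dermatitis (SCORAD) index were 10 and 13.576, respectively". It continues: "The calculation was performed using 80% power, a 5% significance level, and a 10% dropout rate".

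**The concern.** A raw change score carries the rater and day-to-day noise of the single Visit 2 score at full weight. Two things that could reduce that noise are already on the case report form but play no part in the primary comparison: regression of the outcome on the Visit 2 score, and a second score taken a week earlier. Both scores precede randomisation, so using them as covariates cannot bias the comparison. If the entry limit distorts the Visit 1 score, it is expected to do so equally in both arms.

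What is at stake is the width of the confidence interval for the primary contrast in a trial of 66. The validity of that contrast is not in question.

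**Working it through.** **Inputs from the protocol.** Difference 10, SD 13.576, two-sided 5%, 80% power, 10% dropout, 33 per arm.

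**Assumptions.** The protocol gives no visit-to-visit correlations. Write r12, r25 and r15 for the correlations between Visits 1–2, 2–5 and 1–5, and take equal SD at each visit. The protocol does not say whether 13.576 is the SD of the change or of the score; it is taken here as the SD of the change. At r25 = 0.5 the two readings coincide, because 2(1 − 0.5) = 1.

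**1. The plan's own figure.** n = 2(z_α/2 + z_β)² × 13.576² / 10². Unrounded z values give 28.932, as printed; the rounded 1.96 and 0.84 give 28.90. Either rounds up to 29, and 29/0.9 = 32.2, hence 33 per arm and 66 in total. The figure reproduces. Power with 29 evaluable per arm is 80.1% by the normal approximation and 78.7% by the t distribution.

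**2. Adjusting for Visit 2.** In units of the single-visit variance:
- change score: 2 − 2·r25
- residual after regression on Visit 2: 1 − r25²
- ratio: (1 − r25²)/(2 − 2·r25) = (1 + r25)/2

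This is 0.65 / 0.75 / 0.85 at r25 = 0.3 / 0.5 / 0.7. At 0.75 the effective SD is 13.576 × √0.75 = 11.76. The same sample-size formula then gives 28.932 × 0.75 = 21.7, so 22 evaluable per arm instead of 29, and power at 29 per arm is about 90% (normal approximation).

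**3. Adding Visit 1.** Residual variance with both scores: 1 − (r15² + r25² − 2·r12·r15·r25)/(1 − r12²).

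Take correlation decaying with spacing as λ·exp(−t/τ), with lags of 7, 56 and 63 days. At r25 = 0.5 and r12 = 0.7, r15 = 0.477:

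1 − (0.2275 + 0.2500 − 0.3339)/0.51 = 0.718

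That compares with 0.750 for Visit 2 alone, a further cut of 4.2%.

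| Correlation structure | Further cut in residual variance from Visit 1 |
|---|---|
| Decaying, r25 = 0.5, r12 = 0.7 to 0.9 | 4.2% down to 0.1% |
| Decaying, r25 = 0.4 to 0.6, r12 = 0.7 to 0.9 | 0% to 8.5% |
| All correlations equal, 0.3 / 0.5 / 0.7 | 5% / 11% / 17% |
| Pure serial decay, AR(1) | none |

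**4. Cost of the second covariate.** With 66 analysed, residual degrees of freedom go from 64 (t-test) to 63 (Visit 2) to 62 (both). In a simulation with 33 per arm, r12 = 0.8 and r15 = 0.4, where Visit 1 carries nothing beyond Visit 2, power went from 92.3% to 91.5%, a loss of 0.8 points.

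**5. The alternative of averaging Visits 1 and 2 as baseline.** The variance ratio to the planned change score is [1 + (1 + r12)/2 − r15 − r25] / [2(1 − r25)].
- All correlations equal: 0.75.
- Decaying, r25 = 0.5, r12 = 0.7 / 0.8 / 0.9: 0.873 / 0.932 / 0.990.
- AR(1), r25 = 0.3 / 0.5 / 0.7: 0.98 / 1.00 / 1.015.

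Averaging increases the variance whenever r25 − r15 exceeds (1 − r12)/2. Unlike a regression, it imposes equal weights on the two scores.

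**The case against.** The strongest reply is that nothing here is wrong. Baseline is defined once, as the randomisation-day score, and the analysis follows that definition. The sample size assumes no second baseline and reproduces, so the trial keeps its planned power. All of this stands: the point concerns efficiency and is neither an error nor a contradiction.

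A second reply is that most of the gain comes from adjusting for Visit 2, with Visit 1 adding little. This also stands, and the sizes above show it. It is a reason to keep expectations of Visit 1 modest. It does not count against including it, because the regression estimates its weight and the loss when it is uninformative is small.

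Three stronger readings are tempting, and the protocol does not support them.
- *The Visit 1 score is thrown away.* Table 1 places the eligibility check at that visit and entry depends on objective SCORAD. The score has a stated use; it is only absent from the primary analysis.
- *Precision is certainly lost by relying on Visit 2 alone.* That depends on correlations the protocol does not give. Under pure serial decay Visit 1 adds nothing.
- *Baseline should be the mean of the two visits.* Averaging can gain nothing or lose slightly (step 5). DLQI and KiFDA-HM-AD are not scheduled at Visit 1, so SCORAD would have a different baseline from the scales that the Discussion intends to compare it with.

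The entry limit may also narrow the spread at Visit 1, which strains the equal-SD assumption. That bears on averaging more than on the regression, where the Visit 1 increment depends on the correlations and not on the Visit 1 SD.

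**Conclusion.** The planned analysis is valid, conventional and unbiased, but probably less precise than the collected data allow. Replacing the t-test on change with a model for Visit 5 SCORAD adjusted for Visit 2 takes the variance to about 0.75 of its planned value at r25 = 0.5 (0.65 to 0.85 for r25 from 0.3 to 0.7). Visit 1 then contributes a smaller and uncertain amount: 0% to about 8.5% of residual variance under decaying correlations, up to 17% if all correlations are equal, and none under AR(1).

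These sizes rest on assumed correlations and on equal variances across visits; their direction does not. Apart from the small cost of estimating the coefficients, a linear adjustment does not do worse than the raw change score in large samples. It would be wrong to infer that the trial is underpowered or its baseline misdefined. This is a low-cost, optional improvement.

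**What to change.** In the Efficacy assessment section, before unblinding, make the primary analysis a linear model for Visit 5 SCORAD on treatment, with Visit 2 and Visit 1 SCORAD as pre-specified covariates. Report the t-test on change from Visit 2 as a sensitivity analysis. Leave the Primary outcome measurement section's definition of baseline as Visit 2, and do not replace it with the mean of Visits 1 and 2.

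The cost is a change of analysis wording, with no new visit, procedure or participant. Relative to adjusting for Visit 2 alone, the second covariate uses one further degree of freedom, worth under one point of power if Visit 1 proves uninformative.

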### Secondary outcome measurement

Secondary outcome measurements include the change in the Dermatology Life Quality Index (DLQI), the total IgE level, eosinophil counts, IL-4, IL-5, IL-13, TEWL (Transepidermal Water Loss), hydration in the stratum corneum, and KiFDA-HM-AD. The study schedule is detailed in Table 1.

**Table 1 T1:** Study schedule of KM110329 clinical trial (8 weeks)

	**Screening**	**Treatment period**			
	**Visit 1**	**Visit 2**	**Visit 3**	**Visit 4**	**Visit 5**
	**(D − 7)**	**(D 0)**	**(D 7)**	**(D 28)**	**(D 56)**
**Informed consent**	**√**				
**Demographic characteristic eristic**	**√**				
**SCORAD index**	**√**	**√**	**√**	**√**	**√**
**Dermatology Life Quality Index**		**√**	**√**	**√**	**√**
**KiFDA-HM-AD**		**√**	**√**	**√**	**√**
**Laboratory tests**^ **1** ^	**√**	**√**			**√**
**Test for chronic hepatitis**^ **2** ^	**√**				
**Drug use history**	**√**				
**Concomitant medication**	**√**	**√**	**√**	**√**	**√**
**Pregnancy test**	**√**	**√**	**√**	**√**	**√**
**Medical/drug use history**	**√**	**√**	**√**	**√**	**√**
**Adverse event**			**√**	**√**	**√**
**Compliance calculation**			**√**	**√**	**√**
**Inclusion/exclusion criteria check**	**√**				
**Randomisation**		**√**			

^1^CBC (RBC, Hb, Hct, WBC, Platelet, ESR), Immunological tests (Eosinophil, IgE, IL-4, IL-5, IL-13), Liver function tests (AST, ALT), Renal function tests (BUN, Creatinine).

^2^Anti-HBs, HBsAg.

